### 2.5 Randomization and allocation

The random sequence will be generated by the central randomization system from Guangdong Provincial Hospital of Chinese Medicine. Participants will be randomly allocated into either the treatment or placebo group, at a ratio of 1:1. Patients in the treatment group (n = 80) will receive the treatment of SHG, while patients in the placebo group (n = 80) will receive placebo granules, that are identical in appearance to the SHG. Stratified by the central stratification method, we will use SAS 9.2 statistical software to generate random numbers and the random assignment results. The investigators will obtain the randomized number and drug number by a sequential number in the central randomization system. All center numbers, sequence numbers, randomization numbers, and drug numbers will be managed by the statistical unit.

### 2.6 Blinding

This is a double-blind trial in which patients, researchers, outcome assessors, and statistician are all blinded. Blinding codes will be assigned after the randomization operation. This process will be operated by a specially assigned person, and the sequence number of the subject, corresponding random numbers and grouping results will be the primary blinding base. The clinical researcher obtains the subject allocation code through the Internet, and provides corresponding intervention to the subject patient according to the code. Unblinding is permissible in emergency situations when researchers believe that it is necessary to perform any action for patient’s safety. The details of unblinding will be recorded.

### 2.7 Interventions

Both SHG granules and placebo granules will be provided by the Guangzhou Kangyuan Pharmaceutical. The herbal components of Shuhe are shown in Table 1. The chemical fingerprint analysis of SHG were conducted by using an ultra-performance liquid chromatography coupled with Q-exactive Orbitrap mass spectrometry, leading to more than 100 common chemicals peaks. The main ingredients of the placebo are maltodextrin, tartrazine, picrine and lactose. The placebo smell, appearance, taste and weight are consistent with SHG, and will not affect the implementation of blinding. The researcher will administer the drug for 14 days when the participants are enrolled, and again for 14 days during the follow-up visit in the second week. All participants were monitored for 1 day of PSG before and after treatment.

SHG, as a non-decoction granule, should be kept away from direct sunlight to prevent the decomposition or failure of the pharmaceutical ingredients caused by light. Keep the storage environment dry and avoid excessive humidity (relative humidity below 80%) to prevent the granules from absorbing moisture, clumping or mildew. Store in a cool place (generally 10°C–30°C) to avoid changes in drug properties caused by high temperatures. At the same time, SHG will be sealed and stored to prevent the medicine from absorbing moisture in the air or being contaminated by odors, and avoid being stored together with chemical reagents, volatile substances or toxic and harmful substances to avoid adsorbing odors or being contaminated. Regularly check the packaging and appearance of the granules. If any abnormalities such as discoloration, odor, agglomeration, etc., are found, stop use and consult a pharmacist. The sponsor distributes packaging according to random coding, and the usage, batch number, manufacturer and drug number are printed on the outer packaging box.

#### 2.7.1 Intervention group

Patients in the treatment group will receive SHG granules (2 bags at 15 mg each, orally, twice a day, with warm water) for 4 weeks, and the total observation follow-up period will be 8 weeks. In addition, counseling will be provided by research staff about management in insomnia.

#### 2.7.2 Control group

Patients in the control group will receive placebo granules (2 bags at 15 mg each, orally, twice a day, with warm water) for 4 weeks, and the total observation follow-up period will be 8 weeks. In addition, counseling will be provided by research staff about management in insomnia.

If the participants’ condition has not improved during the clinical trial, the life and work are affected, or emotional changes, we will maintain a good communication with the patients, and give the temporary western medicine temporarily with the consent of fully knowledge. We will instruct patients on how to take medication and what precautions to take, and make a registration for taking medication. Observation for 1 week, during the medication, we will still to observe the changes in the condition at any time, and fall off when necessary. If the ISI remains unchanged or increased, but the GAD-7 and PHQ-9 scores increase ≤4 points, Stilnox 10 mg will be administered on an as-needed basis. Conversely, if the GAD-7 or PHQ-9 scores increase by ≥5 points, or if the anxiety and depression factor scores on the Symptom Checklist-90 are severe, Lorazepam 1 mg will be administered on an as-needed basis.

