### 2.2 Trial design

This is a single-center, randomized, double-blind, parallel group, placebo-controlled clinical trial. The trial will be conducted in the Guangdong Provincial Hospital of TCM. A total of 160 eligible participants will be randomized into the experimental group (SHG) or the control group (placebo) with a 1: 1 ratio. The duration of the intervention is 4 weeks and the total observation follow-up period will be 8 weeks. Study visits will take place at baseline and at 2, 4, 6, 8 weeks. Each patient will be asked to visit within 3 days of the given time point. All participants will be required to sign the written informed consent (Supplementary Material 6, 7) before randomization. This protocol was compiled in line with the Standard Protocol Items: Recommendations for Interventional Trials (SPIRIT) Guidelines (Supplementary Material 8; Chan et al., 2013). The flowchart of this trial is presented in Figure 1. The schedule of enrollment, interventions, and assessments is as shown in Table 2.

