#### 2.4.5 Withdrawal/termination criteria

Participants will be withdrawn or terminated from the trial if they meet any of the following criteria:(1). Serious adverse events are reported at any time, and patients are unable to continue.(2). Patients who present with serious changes or complications related to the disease during the trial.(3). Patients who cannot comply with the instructions and follow-up procedures of this trial, leading to incomplete medical administration records, or patients who took banned drugs or other medications that may interfere with the efficacy and safety evaluation of this study.(4). Patients who request to be withdrawn from the trial.

Besides, researchers will record the last time of drug intake and collect evaluation items of participants who discontinue or deviate from intervention protocols.

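### Rescue medication given under section 2.7.2 falls within withdrawal criterion (3), and its score triggers cannot be evaluated from the visit schedule before week 4

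*Protocol article*

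**What the plan says.** **Rescue (section 2.7.2).** The paragraph opens with "If the participants’ condition has not improved during the clinical trial" and provides for temporary conventional medication, with consent, a record of use and a week of observation. Two score rules follow. The first is "If the ISI remains unchanged or increased, but the GAD-7 and PHQ-9 scores increase ≤4 points, Stilnox 10 mg will be administered". The second leads to Lorazepam, "if the GAD-7 or PHQ-9 scores increase by ≥5 points, or if the anxiety and depression factor scores on the Symptom Checklist-90 are severe". On what happens to the participant meanwhile, it says "we will still to observe the changes in the condition at any time, and fall off when necessary".

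**Withdrawal (section 2.4.5).** The list is introduced by "Participants will be withdrawn or terminated from the trial if they meet any of the following criteria". Criterion (3) includes "patients who took banned drugs or other medications that may interfere with the efficacy and safety evaluation of this study". The section closes by asking for evaluation items from those who discontinue or deviate, without naming visits.

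**Schedule (section 2.2 and Table 2).** "The schedule of enrollment, interventions, and assessments is as shown in Table 2". ISI is ticked at baseline and weeks 2, 4, 6 and 8. GAD-7 and PHQ-9 are ticked at baseline, week 4 and week 8. The Symptom Checklist-90 has no row.

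**Placement.** The rescue paragraph is printed under 2.7.2 Control group. Section 2.7.1 on the intervention group has dosing and counselling only. Section 2.6 blinds patients, researchers, assessors and statistician.

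**The concern.** Two sections give different instructions for the same event. A participant who receives a hypnotic or benzodiazepine from trial staff is, under section 2.7.2, normally followed on. Under section 2.4.5 the same participant has taken medication that may interfere with the evaluation of a sleep outcome and is to leave. Two investigators could act in opposite ways and both be following the protocol.

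This bears on the primary endpoint because a failure of ISI to improve is part of the first trigger, and the primary outcome is the change in ISI at 4 weeks. Rescue is therefore likely to be commoner in the arm that does worse. If rescued participants leave, the missing week-4 values cluster among non-responders. Section 2.11 would fill them by a linear trend or, failing that, by last observation carried forward; neither, as described, takes account of why the value is missing. If they stay, the week-4 ISI contains the effect of the rescue drug, which narrows the difference between the arms.

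The triggers raise a second problem: staff are asked to act on score changes that the visit schedule does not supply during most of the treatment period.

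**Working it through.** The plan gives no figure on this point, so the check is mainly one of text against text.

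**Step 1: rescue against withdrawal.** Section 2.7.2 makes dropping the participant conditional on necessity, so staying is the default. Section 2.4.5 makes withdrawal follow from meeting any one criterion. Criterion (3) covers interfering medication in general and does not exempt medication given by the trial itself. A sleep or anxiety drug taken before an ISI assessment fits that description by plain meaning. The defaults are opposite.

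**Step 2: triggers against Table 2.**

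| Score named in the rules | Baseline | Wk 2 | Wk 4 | Wk 6 | Wk 8 |
|---|---|---|---|---|---|
| ISI | yes | yes | yes | yes | yes |
| GAD-7 | yes | no | yes | no | yes |
| PHQ-9 | yes | no | yes | no | yes |
| Symptom Checklist-90 | no | no | no | no | no |

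Week 2 is the only scheduled visit between baseline and the end of treatment. Of the four scores, only ISI is available then. The first rule needs ISI together with GAD-7 and PHQ-9 changes; the second needs a GAD-7 or PHQ-9 change, or the Symptom Checklist-90. From scheduled data, neither rule, nor the choice between the two drugs, can be evaluated before week 4, which is the primary endpoint visit.

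**Step 3: placement.** The heading says control group, the text says participants, and staff are blinded to arm. A rule for one arm could not be operated under that blinding.

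**Step 4: what the size could be, under assumptions only.** Section 2.10 gives 128 patients before inflation for loss, and 128 / (1 − 0.20) = 160 reproduces the planned enrolment. So take 64 evaluable per arm. Assume a one-sided alpha of 0.025 and the standardized difference d that gives 80% power:

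d = (1.960 + 0.842) × √(2/64) = 0.495.

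*Retained.* Assume that rescue improves ISI by as much as the assumed SHG effect. With rescue proportions c (placebo) and t (SHG), the difference becomes d × (1 − (c − t)).

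| c | t | Power |
|---|---|---|
| 10% | 0% | 71% |
| 20% | 0% | 61% |
| 30% | 0% | 50% |
| 10% | 5% | 76% |
| 20% | 10% | 71% |
| 30% | 15% | 66% |

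*Withdrawn.* If total loss rises from 20% to 25%, 30% or 40%, the number per arm is 80 × (1 − loss) = 60, 56 or 48, and power is about 77%, 75% or 68%. This counts lost numbers only; bias from selective loss comes on top and is not quantified.

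The proportions and the rescue effect are invented to show a range. The retained scenario also requires rescue before week 4, which by step 2 could come only from unscheduled assessments or from the paragraph's general opening condition.

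**The case against.** Several points on the other side have force.

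- *The specific rule may govern.* Section 2.7.2 describes supervised, consented and registered rescue, and can be read as an implied exception to criterion (3). That section names no hypnotic, and no list of banned drugs is shown. The reading is reasonable, but nothing states it, and criterion (3) is worded as automatic.
- *A reader might infer that only placebo patients can be rescued, with bias and unblinding as a result.* The documents do not support this. The paragraph speaks of participants, and blinded staff could not apply a one-arm rule. What stands is a misplaced paragraph.
- *A reader might infer that the rules cannot work at all.* That goes too far. Section 2.7.2 provides for observing the condition at any time, Table 2 does not forbid unscheduled assessments, GAD-7 and PHQ-9 are available at weeks 4 and 8, and the Symptom Checklist-90 is only an alternative trigger. The narrower statement about scheduled data before week 4 stands.
- *Part of the remedy is already there.* Rescue use is to be registered, and evaluation items are to be collected after discontinuation. This stands, although the visits are not named.
- *A reader might infer that rescued values will be analysed as if no rescue had occurred.* The documents do not say so. Section 2.11 commits to the intention-to-treat principle, and further handling may be in an analysis plan that is not shown.
- *The size is assumed.* This is correct. Where rescued participants are retained and rescue is commoner on placebo, the effect is dilution towards no difference, not a false claim of benefit.

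**Conclusion.** Sections 2.4.5 and 2.7.2 and Table 2 contradict each other on rescue medication and are wrong as written. Three things are established from the text. Retention and withdrawal are both prescribed for the same participant, on the plain meaning of criterion (3). The score rules cannot be evaluated from scheduled data before the primary endpoint visit. The rescue paragraph stands under the wrong heading, most likely as a drafting slip.

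The consequence for the primary analysis is real in direction but unknown in size, because the documents give no rescue rate. The power figures above illustrate a range and are not an estimate. Outcome-dependent loss is the more serious of the two possibilities, because ISI values that were not collected cannot be recovered later, whereas values collected after rescue leave the choice of analysis open.

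**What to change.** Reconcile sections 2.4.5, 2.7.1 and 2.7.2 with Table 2 on three matters: whether rescue leads to withdrawal, to whom the rescue paragraph applies, and how the scores that it names relate to the visits at which they are measured. Which clinical rule to keep is for the investigators and the ethics committee; no view is taken here.

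Whichever rule is kept, state that ISI continues to be collected at the scheduled visits from every rescued or discontinued participant, and that these values enter the week-4 intention-to-treat analysis. Report rescue use by arm, drawing on the medication record that section 2.7.2 already requires. A supplementary analysis that counts rescued participants as unimproved is optional.

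The cost is a protocol clarification and possibly an ethics notification. Including values obtained after rescue accepts some dilution of the estimated difference; the optional analysis would show how much the result depends on it.

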### 2.8 Outcomes and measurements

The time points of the study data collection for outcome measurements are shown in Table 2.

#### 2.8.1 Primary outcome

The primary outcome is the change of ISI score after 4 weeks of intervetion.

ISI consists of seven items, with scores ranging from 0 to 4 for each item, and total scores ranging from 0 to 7 indicating normal sleep, from 8 to 14 indicating mild insomnia, from 15 to 21 indicating moderate insomnia, and from 22 to 28 indicating severe insomnia (Cerri et al., 2023).

#### 2.8.2 Secondary outcomes

Secondary outcomes are the following:1). Pittsburgh Sleep Quality Index (PSQI). The PSQI is an internationally established tool that is used to evaluate sleep quality. The scale includes seven dimensions that consist of subjective sleep quality, sleep latency, sleep duration, habitual sleep efficiency, sleep disturbances, sleeping medication and daytime dysfunction. The score correlates adversely with sleep quality which a higher score means the sleep quality is worse, and each factor has a score of 0–3 to provide a total score of 21 points (Buysse et al., 1989; Mollayeva et al., 2016).2). Fatigue severity scale (FSS). FSS is used to measure the degree of fatigue in patients with various diseases and impaction on people’s activities and lifestyles. It has a total of 9 items, each scored on a scale of 1–7, with higher scores being associated with greater fatigue (Kim et al., 2019).3). Patient Health Questionnaire (PHQ-9). PHQ-9 consists of nine items, with scores ranging from 0 to 3 for each item, and total scores ranging from 0 to 4 points indicating no depression, from 5 to 9 points indicating mild depression, from 10 to 14 points indicating moderate depression, from 15 to 19 indicates moderate to severe depression, and from 20 to 27 indicates severe depression.4). Generalized Anxiety Disorder (GAD-7). GAD-7 consists of 7 items, each item scores range from 0 to 3 points, the total score ranges from 0 to 4 points indicating no clinical significance of anxiety, from 5 to 9 points indicating mild anxiety, from 10 to 14 points indicating moderate anxiety, and more than 15 points indicating severe anxiety. A total score of 10 or more may indicate anxiety disorder.5). Polysomnography (PSG). All PSGs are tested using the Australian Kandi Somte-PSG System, including electroencephalogram, electromyogram, eye movements, electrocardiogram, respiratory airflow, snoring, chest and abdominal movements, leg movements, blood oxygen saturation, and pulse rate. Use the above parameters to perform sleep staging, discover and evaluate sleep apnea, and parasomnias (Boulos et al., 2019).

### 2.9 Safety assessments

The interventions will be carried out under the guidance of a researcher. The herbs in the SHG are safe in accordance with the recommended amount in Chinese Pharmacopoeia. We will closely observe the physical conditions and subjective description of the participants. Blood, urine and electrocardiogram analysis as well as liver and kidney function tests will be performed before enrollment and at 4 weeks after enrollment. All adverse events will be recorded on the case report forms (CRFs) and reported to the principal investigator. Any severe adverse events will be reported to the Ethics Committee of Guangdong Hospital of Traditional Chinese Medicine within 24 h. The committee of medical experts will determine whether adverse events are related to the SHG. Guangdong Hospital of Traditional Chinese Medicine will cover the cost of treatment and the corresponding economic compensation for the damage related to the trial. Participants have the right to withdraw their consent to participate in the study at any time for any reason. Other unintended effects of study interventions and study conduct will also be recorded and reported.

### 2.10 Sample size calculation

The sample size is calculated based on the primary endpoint (the changes in ISI). According to the previous exploratory clinical trial (unpublished), the effect size of the treatment group was 24.3%, with a power of 0.8 and alpha of 0.025, a total of 128 patients should be included to detect a difference in ISI score between the SHG and placebo groups. To account for a 20% loss to follow-up, at least 160 patients (80 patients in each group) are planned to be enrolled.

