*Ophiopogon japonicus (Thunb.) Ker Gawl*. [Asparagaceae]	10	Dried root
*Morinda officinalis* How [Rubiaceae]	10	Dried root

Our early single-arm pilot RCT of 62 participants showed that following a 2-week of SHG intervention, the Insomnia Severity Index (ISI) decreased by 15.38%, resulting in an average score reduction of 4.42 points. Additionally, the Pittsburgh Sleep Quality Index (PSQI) decreased by 16.23%, with an average score reduction of 2.63 points. Our findings suggest that ISI may be a more reliable indicator of the effectiveness of SHG compared to PSQI. No adverse events (AEs) were reported. However, there is currently insufficient evidence from evidence-based trials to support the widespread use of SHG for treating insomnia. As a result, we are planning to conduct a well-designed, randomized double-blind controlled clinical trial to further investigate the efficacy and safety of SHG in the treatment of chronic insomnia.

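### The 80% power claimed for 128 evaluable patients is not supported by the stated 24.3% effect size, which has no metric, between-group difference, SD or sidedness

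*Protocol article*

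**What the plan says.** Section 2.10 takes its effect from an earlier study: "According to the previous exploratory clinical trial (unpublished"). The effect, the error rates and the resulting total are given together: "the effect size of the treatment group was 24.3%, with a power of 0.8 and alpha of 0.025, a total of 128 patients". The conclusion concerns a two-group contrast: "a total of 128 patients should be included to detect a difference in ISI score between the SHG and placebo groups". A 20% loss to follow-up then brings the total to 160, or 80 per arm.

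The Introduction describes the only earlier study with figures: "Our early single-arm pilot RCT of 62 participants", read after 2 weeks of SHG. Its ISI result is that "the Insomnia Severity Index (ISI) decreased by 15.38%, resulting in an average score reduction of 4.42 points".

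Section 2.8.1 makes the primary outcome the change in ISI after 4 weeks and gives the top band of the scale as "from 22 to 28 indicating severe insomnia". Section 2.11 plans analysis of covariance with a Bonferroni correction and, as its example, tests ISI at 0.05/3 = 0.0167. The Discussion says the sample size rests on the previous exploratory study and that this may overestimate efficacy.

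**The concern.** The power of a two-arm comparison of means depends on the difference between the arms divided by the SD. Section 2.10 gives neither, nor a placebo response from which a difference could be formed. Its single effect figure is attached to the treatment group. A change within one arm also contains placebo response and regression to the mean, so it cannot by itself power a comparison with placebo.

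The most direct reading of a bare effect size of 24.3%, a standardised difference of 0.243, leads to a sample about four times the one stated. The sidedness of alpha is open as well, and section 2.11 uses a third threshold for the same scale.

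The stake is how the result will be read. If the trial shows no difference, nobody can say which difference it had 80% power to detect, so a null result could not be interpreted.

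**Working it through.** **Inputs.** From section 2.10: effect 24.3%, power 0.80, alpha 0.025, total 128 (64 per arm), 20% loss. Allocation is 1:1 (section 2.2). From the Introduction: a fall of 15.38%, or 4.42 points. ISI maximum 28 (section 2.8.1). Threshold 0.0167 (section 2.11). All sample sizes and powers below are for a two-sample t-test. One-sided 0.025 and two-sided 0.05 are treated as the same test.

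**1. Loss to follow-up.** 128 / (1 − 0.20) = 160. This step is correct.

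**2. What difference does 128 correspond to?** The approximate formula is n per arm = 2(z_alpha + z_power)² / d². With d = 0.50 at one-sided 0.025: 2 × (1.960 + 0.842)² / 0.25 = 62.8. The exact t-test gives 63.8, so 64 per arm and 128 in total. This reproduces the stated figure, but 0.50 appears nowhere in the article. Solved the other way, 64 per arm gives 80% power for d = 0.499 at one-sided 0.025 and for d = 0.551 at two-sided 0.025.

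**3. Readings of 24.3%.**

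| Reading | Total at one-sided 0.025 | Total at two-sided 0.025 |
|---|---|---|
| Standardised difference 0.243 | 534 (266.8 per arm) | 648 (323.2 per arm) |
| Correlation r = 0.243 | 128 (63.5 per arm) | 156 (77.002 per arm) |
| Unstated d = 0.50 | 128 (63.8 per arm) | 156 (77.3 per arm) |

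The correlation is converted by d = 2r / √(1 − r²) = 0.486 / √(1 − 0.0590) = 0.501.

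If 0.243 is a standardised difference, power at two-sided 0.05 is 28% with 64 per arm and 33% with 80 per arm. At two-sided 0.025 it is 19% with 64 per arm.

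Read as a difference in proportions, 24.3 points gives 128 only at particular control rates (for example 0.30 or 0.45 at one-sided 0.025, without continuity correction). None is stated, and the endpoint is continuous.

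Read as a percentage fall from baseline, the total depends entirely on values the article does not give. With an assumed baseline of 18.2, it runs from 26 (placebo fall 0%, SD 4) to 396 (placebo fall 15%, SD 6), by the normal approximation at one-sided 0.025.

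**4. Power for d = 0.50 with 64 per arm, by threshold.**

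| Threshold | Power |
|---|---|
| Two-sided 0.05 | 80% |
| Two-sided 0.025 | 71% |
| Two-sided 0.0167 | 66% |

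With all 160 evaluable, 80% power at two-sided 0.05 is reached for d of about 0.45.

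**5. The pilot figures.** A mean fall of 4.42 points that is 15.38% of the baseline mean gives 4.42 / 0.1538 = 28.74. Rounding allows 4.415 / 0.15385 = 28.70 to 4.425 / 0.15375 = 28.78, all above 28. The PSQI pair in the same paragraph is coherent: 2.63 / 0.1623 = 16.2 on a 21-point scale. For comparison, 4.42 / 0.243 = 18.2, which is a possible ISI baseline. That is suggestive only.

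**The case against.** The strongest objection is that one reading of 24.3% does give 128: as a correlation it converts to d = 0.501 and reproduces the total exactly at one-sided 0.025. A reader might infer from the 534 that the sample size is simply wrong, and the documents do not support that. What can be shown is an undefined input, not a wrong total. The correlation reading does not rescue the paragraph either. No correlation is named, it is a two-group quantity while the figure is attached to the treatment group, and it works only if alpha is one-sided.

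A reader might also infer that 24.3% is a one-arm change from the Introduction's pilot and contradicts its 15.38%. This is not established. No section says that the two figures share a study, time point or metric, and the Introduction calls the pilot both single-arm and an RCT. The figures are unreconciled, which is a weaker statement.

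The impossible baseline assumes a ratio of means. If percentages were averaged patient by patient, the average could be no less than 4.42 / 28 = 15.8% unless some patients worsened. So 15.38% could arise that way, but the article does not describe such a calculation.

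Two further points stand in part. The planned analysis of covariance would raise power: at an assumed baseline-outcome correlation of 0.5, with the SD read as the outcome SD, the 28% and 33% become about 35% and 42%. The Discussion does warn of overestimation, but that warning supplies no between-group difference. The article is condensed, so a missing SD alone would be a weak point. Here, however, a calculation is presented and its stated input does not lead to its stated result.

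**Conclusion.** The concern holds in this form: the 80% power with 128 evaluable patients is not supported by the input given for it. The total fits an unstated standardised difference of about 0.50 at one-sided 0.025. Across the standardised readings checked, power at 64 per arm runs from 19% (0.243, two-sided 0.025) to 80% (0.50, two-sided 0.05). These figures assume an unadjusted two-sample t-test and 1:1 allocation; covariate adjustment would improve them by an amount the article does not allow one to fix. The 28% applies only if 24.3% is a standardised difference, and is not an estimate of the trial's actual power.

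The pilot's ISI pair is a real but secondary error: read as a percentage of the baseline mean, it puts that mean about 0.7 points above the top of the scale. It is not shown to be an input to the sample size.

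**What to change.** Keep 160 patients and rewrite section 2.10:

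- Replace the 24.3% with the assumed SHG-placebo difference in 4-week ISI change, in points, with its SD and the source of both. A difference of 0.50 SD should not be adopted merely because it returns 128; it needs its own justification.
- State whether alpha is one- or two-sided, and make it agree with the 0.0167 threshold that section 2.11 gives for ISI.
- State what the design delivers at the chosen threshold. For d = 0.50 with 128 evaluable, that is about 80%, 71% or 66% power at two-sided 0.05, 0.025 or 0.0167. With all 160 evaluable at two-sided 0.05, it is 80% power for d of about 0.45.
- In the Introduction, correct the 15.38% and 4.42-point pair from the pilot data, and say whether that pilot is the exploratory trial cited in section 2.10. If it is, say that it was uncontrolled and read at 2 weeks.

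The cost is the rewording of two paragraphs, with section 2.11 brought into line on alpha, and no additional patients. The downside is that the stated power may become less favourable than 80%.
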